## **10. Handling and storage of data and images**

*10.1 Describe how subject's privacy is protected. Describe how, when and by whom data is coded, and how the key table is safeguarded.*

Samples from the abortion clinic and samples from the Fetal Biobank are shared with us anonymously and therefore privacy of these participants is guaranteed. Placental samples obtained at the Erasmus MC will be coded by the researcher before DNA isolation from samples and data-analysis will be performed. The key to the study-ID's is kept separately and remains on site with the local research team.

*10.2 Describe how data is stored (i.e. which data management system/data capture system), who has access to the coded source data, how long data will be kept, which steps are taken to ensure data security, what happens with the data after the research has been completed.*

Data will be stored at secured servers at the Erasmus MC. Study documents and tissue samples are stored for 15 years after the end of the study. The only individually identifiable information collected is patient's ID for samples collected at the Erasmus MC and this information is kept separately from the research data and is only accessible to the research team, the study monitor, and Inspectie Gezondheidszorg en Jeugd (IGJ). The handling of personal data will comply with the EU General Data Protection Regulation and the Dutch Act on Implementation of the General Data Protection Regulation (in Dutch: Algemene Verordening Gegevensbescherming en Uitvoeringswet Algemene Verordening Gegevensbescherming).

*10.3 Describe how images are stored, how the subject's privacy is protected, what happens with images after the research has been completed.*

Not applicable

*10.4 Describe how approval of re-use of data and/or images is obtained.*

No (additional) approval will be obtained from participants who already provided informed consent or for samples retrospectively collected at the Erasmus MC. For women recruited prospectively at an abortion clinic or at the Erasmus MC, approval of re-use of data will be asked via the IC form.

## 11. Handling and storage of human material

*11.1 Please describe which human material is used.*

Placental tissues collected from different trimesters.

*11.2 Check all the boxes which are applicable to the human material origin:*

- ☒ Regular clinical care
- ☒ Research
- ☒ Left-over human material

## Placental Methylation

- ☐ De Novo biobank material
- ☐ Other, *please specify*

### 11.3 How is human material handled and stored?

- ☒ Anonymous, i.e. the material can never be traced back to an individual subject
  - ➔ This is the case for samples collected at the Fetal Biobank Amsterdam and abortion clinics
- ☒ Pseudonymised/Coded
  - ➔ This is the case for samples collected at the Erasmus MC
- ☐ Identifiable

### 11.4 *In case of new human material collection, describe how the human material is coded and stored (which registration system, Central Biobank or other location), who has access to the registration system and human material, by whom the key to the code is safeguarded, how long and where human material will be kept, what happens with the human material after the research has been completed.*

Newly collected placental samples from the abortion clinic will be shared with us anonymously and will be given a random study ID. Newly collected samples at the Erasmus MC will also be coded before storage. The key to the code remains on site with the local research team. Newly collected tissues will be stored at the local research department for 15 years. The research team has access to the registration system and materials. After 15 years the material will be destroyed.

### 11.5 *Describe how approval for re-use of human material is obtained.*

No (additional) approval will be obtained from participants who already provided informed consent or for samples retrospectively collected at the Erasmus MC. For women prospectively recruited at an abortion clinic or at the Erasmus MC, approval of re-use of their materials will be asked via the IC form.

## 12. Amendments

Amendments are changes made to the research after a favourable opinion by the NWTC has been given. All amendments must be submitted to the NWTC that gave the favourable opinion. Substantial amendments must be approved by the NWTC before they can be implemented

## 13. Publication

Do you have the intention to submit the study results in a manuscript for publication in a journal:

- ☒ Yes  
☐ No, *please motivate*

## LIST OF ABBREVIATIONS AND RELEVANT DEFINITIONS\*

|                          |                                                                                                                                             |
|--------------------------|---------------------------------------------------------------------------------------------------------------------------------------------|
| cfDNA             | Cell free DNA                                                                                                                               |
| DMR               | Differentially Methylated Region                                                                                                            |
| Exception consent | Form Care for data Template , in Dutch: Formulier uitzondering toestemming                                                                  |
| FDR               | False Discovery Rate                                                                                                                        |
| IC                | Informed Consent                                                                                                                            |
| MEC               | Medical Ethics Committee                                                                                                                    |
| MeD-seq           | Methylated DNA sequencing                                                                                                                   |
| NIPT              | Non-invasive prenatal testing                                                                                                               |
| NWTC              | Non-WMO Review Committee; in Dutch: Niet WMO Toetsingscommissie                                                                             |
| UAVG              | Dutch Act on Implementation of the General Data Protection Regulation;
in Dutch: Uitvoeringswet Algemene Verordening Gegevensbescherming |
| WMO               | Medical Research Involving Human Subjects Act, in Dutch: Wet Medisch-wetenschappelijk Onderzoek met Mensen                                  |

## PROTOCOL SUMMARY

DNA methylation plays a vital role in placental development and methylation differences are associated with multiple placental related complications. Placental-originated cell free DNA (cfDNA) circulates in maternal plasma, providing the opportunity to non-invasively study placental DNA methylation during pregnancy. Up until recently, cfDNA was already widely used for non-invasive prenatal testing (NIPT) on a trial base (TRIDENT-2 study) and cfDNA screening is currently implemented in regular health care.

We aim to identify differentially methylated regions (DMRs) in cfDNA from residual NIPT samples between women who at a later gestational age developed preeclampsia (group 1), intrauterine fetal growth restriction (group 2) and spontaneous preterm birth (group 3) all as compared to uncomplicated pregnancies (group 4). Included women who delivered at the Erasmus MC and/or participated in The Rotterdam Periconception Cohort (PREDICT study, MEC-2004-227) will retrospectively be selected..

We will use the Methylated DNA sequencing (MeD-seq) technology to identify DMRs genome-wide. MeD-seq requires a limited amount of input DNA and is therefore compatible with the low levels of cfDNA available in clinical practice. Based on previous experiments to generate reference profiles using MeD-seq, the number of identified DMRs stabilizes when having samples from ten different individuals. Therefore, to prevent the identification of unreliable DMRs (related to genomic variation), we intend to include twenty patients per group (training and validation set), with a total of four groups in this pilot study.

Since suboptimal implantation and placentation in the beginning of pregnancy is involved in the pathophysiology of placental related complications, we hypothesize to identify disease-specific DMRs already present at the end of first trimester. NIPT sampling is usually performed between 11 and 13 weeks of gestation. Identified DMRs can potentially serve as biomarkers able to predict disease risk.

Second, we aim to identify underlying genes or genetic pathways related to identified DMRs involved in disease development, improving our understanding of underlying pathophysiology. This study could potentially lead to an expansion of current NIPT (Epi-NIPT), and initially will serve as a validation cohort for future studies into cfDNA.

There will be no additional burden or risks for participants, since our study focusses on material and data already collected (in both TRIDENT-2 as the Predict study).

## 1. Introduction and rationale

Impaired placenta development is involved in the causality of important obstetric complications, including preeclampsia and intrauterine growth restriction, resulting in increased maternal and fetal morbidity and mortality.(1, 2) DNA methylation is an important epigenetic mechanism involved in the (re)programming of gene expression and plays a vital role in placental development.(3-5)

Emerging evidence indicates a role for DNA methylation in the development of different placental related complications, either as cause or consequence. We and others have shown DNA methylation differences in postpartum placental tissues between pregnancies complicated by different placental related diseases, including preeclampsia, intra-uterine growth restriction and preterm birth as compared to controls.(6-13) For example, using the Illumina HumanMethylation450K beadchip technology Herzog *et al.* identified 869 differentially methylated positions in postpartum placental tissues between pregnancies diagnosed with preeclampsia <34 weeks of gestation compared to preterm birth controls.(12) DNA methylation differences associated with placental related complications could provide more insight in underlying pathophysiology. Moreover, disease-specific DNA methylation differences could potentially serve as biomarkers, ideally able to predict the risk of associated diseases at an early stage when targeted preventative interventions are most effective.(14)

Previous DNA methylation studies mainly focussed on postpartum placental tissues. (6-13) However, cfDNA originating from turnover of placental cell types circulates in maternal plasma providing the exciting opportunity to study placental DNA methylation in a non-invasive manner already during pregnancy.(15) cfDNA is currently already widely used for non-invasive prenatal testing of aneuploidies.(15) Between April 2017 and April 2023, all pregnant women in the Netherlands were offered NIPT on a trial basis (TRIDENT-2 study) and the NIPT uptake increased to over 40% in 2018.(16, 17) At the Erasmus MC, residual NIPT samples collected in the last two years are stored at the department of clinical genetics. Last month, promising results were reported by others who also used residual NIPT samples, indicative of cfDNA methylome profiling as promising tool for the prediction of early onset preeclampsia which could improve future obstetric care.(18)

The Rotterdam Periconception Cohort (PREDICT study, MEC-2004-227) is an ongoing cohort study longitudinally following women during pregnancy from the periconception period onwards. (19, 20) Moreover, a new subcohort is embedded in the Predict study in which longitudinally cfDNA will be collected to study DNA methylation profiles in relation to placental related complications. DNA methylation profiles related to preeclampsia, intrauterine growth restriction or spontaneous preterm birth identified in NIPT samples can serve as a validation cohort for the new prospective subcohort study.

From the different methods to study genome-wide DNA methylation, we will use MeD-seq technology. MeD-seq requires a limited amount of input DNA and is therefore one of the few technologies compatible with the low levels of cfDNA available in clinical practice.(21) Besides, MeD-seq analyses focusses on regional

changes in DNA methylation, requiring less sequencing depth as compared to whole-genome bisulfite sequencing while providing a more extensive coverage of the genome as widely used microarrays or reduced representation bisulphite treatment.(22, 23)

In summary, we aim to identify DMRs in cfDNA from residual NIPT samples between women who at a later gestational age developed preeclampsia, intrauterine growth restriction or spontaneous preterm birth as compared to uncomplicated pregnancies. We intend to identify underlying genes or genetic pathways related to identified DMRs, hereby increasing our understanding of underlying pathophysiology. Identified DMRs can potentially serve as biomarkers able to predict placental related disease risk early in pregnancy. In the future, this could potentially lead to an expansion of current NIPT (Epi-NIPT). Moreover, this study will serve as a validation cohort for our future prospective subcohort.

## 2. Objective(s)

1. Identify specific DMRs in first trimester residual NIPT samples related to adverse pregnancy outcome such as preeclampsia, intrauterine growth restriction and spontaneous preterm birth.
2. Identify underlying genes or genetic pathways related to identified DMRs, involved in disease development.
3. Create a validation cohort of DMRs in cfDNA for prospective subcohorts.

## 3. Study type

### 3.1 Study type:

- ☒ Retrospective  
☐ Prospective  
☐ Combination Retrospective/Prospective

### 3.2 Check all the applicable boxes:

- ☒ Medical records (re-use of data from healthcare, including AI)  
☐ Case report  
☒ Re-use data from research  
☐ Evaluations of quality of healthcare (retrospective)  
☐ Research with additional use of residual material from regular healthcare  
☒ Research with re-use of human materials from research or existing biobank  
☐ Research with human materials without biobank

- ☐ De novo biobank (human material obtained without burdensome or invasive procedures)
- ☐ Post marketing survey research with medical devices
- ☐ Phase IV research
- ☐ Healthcare evaluation research (prospective)
- ☐ Medical devices
- ☐ In Vitro Diagnostic Tests
- ☐ Other research, *describe*

#### 4. Study population

##### 4.1 Population (base)

Eligible women participated in the TRIDENT-2 study and during the same pregnancy participated in the Predict study and/or delivered at the Erasmus MC Rotterdam.

Women who developed preeclampsia, intrauterine growth restriction or spontaneous preterm birth will be included and compared to controls with an uncomplicated pregnancy. We aim to include samples from twenty women per group (total n=80).

##### 4.2 Inclusion criteria

In order to be eligible to participate in this study, a subject must meet all of the following criteria:

- Participated in the Predict study or delivered at the Erasmus MC Rotterdam.
- Participated in the TRIDENT-2 study during the same pregnancy and agreed with the use of residual material for research purposes.
- At least 18 years of age at the time of participating in above mentioned studies.
- Developed preeclampsia (n=20) or intrauterine growth restriction (n=20) or delivered spontaneously preterm (n=20) or had an uncomplicated pregnancy (n=20).

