**Implementation**

During thirty months, after approval of this addendum and informed consent from the participants, additional blood draws will be performed at the same day as the ultrasound visits for the Predict study around 11, 22-24 and 30-32 weeks of gestation and during delivery if the delivery takes place at the Erasmus MC. This blood draw at 11 weeks of gestation will be combined with the current blood draw in

first trimester which is already being performed within the Predict study. Two extra tubes of blood will be collected in CellSave tubes and processed into plasma to be stored at -80°C until isolation of cfDNA takes place.

Our primary outcome are differentially methylated regions (DMRs) found in these cfDNA methylation profiles between uncomplicated controls versus women who develop pregnancy related diseases like pre-eclampsia, intra-uterine growth restriction and pre-term birth. It is not possible to make a power calculation beforehand because it is not known what the methylation profiles will look like. However, based on previous experiments to generate reference profiles using MeD-seq, the number of reliable DMRs stabilizes when having a sample size of  $\pm 8-9$  samples. The incidence of the above mentioned pregnancy related diseases in Europa are 4-5% for pre-eclampsia (27), 9% for preterm birth (28) and 8-10% for intra-uterine growth restriction (29). We aim to include 10 pre-eclampsia cases and account for 20-25% loss to follow up, including loss because of miscarriages. Therefore we intend to include 300 women in total. Because of the higher incidence of preterm birth and intra-uterine growth restriction it is likely this cohort will comprise at least 10 women affected by these complications as well.

We will identify specific DMRs in cfDNA from maternal plasma determined using MeD-seq and perform pathway analyses of genes associated with identified DMRs involved in associated diseases using <http://geneontology.org> in collaborations with the department of Developmental Biology, [name], Erasmus MC.

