## 5. Methods

### 5.1 *Please describe how you do conduct research and which methods are used, e.g. questionnaires, human material collection, extraction of data from medical records, analysis of images, the use of an app/medical device/diagnostic test, clinical tests to be performed, etc. Include information on frequency, duration, volumes, if a Data Management Plan is available (then please upload DMP).*

This study will use data previously collected in the Predict study, medical records, and blood samples previously collected for NIPT in the TRIDENT-2 study. Participation in the TRIDENT-2 study will be checked for Predict participants and for eligible patients who had complicated deliveries at the Erasmus MC Rotterdam in the last two years in collaboration with the Clinical Genetics Department at the Erasmus MC. Cases and controls will be selected until twenty patients in each group are selected. The MeD-seq technology will be used to investigate DNA methylation profiles in cfDNA between women who developed preeclampsia, intrauterine growth restriction or spontaneous preterm birth compared to uncomplicated control pregnancies. Custom Python scripts will be used to process the acquired DNA methylation profiles. Raw data files (fastq) will be filtered to be able to distinguish methylation data from background data and will be mapped to the human genome (hg38) using bowtie. To subsequently analyse DMRs, we will generate both regional (promoter, gene body and CpG Island regions) as genome-wide methylation scores. For the genome wide analysis, a sliding window technique will be used to detect DMRs. The Chi-squared test will be used for statistical testing with either the False Discovery Rate (FDR) or Bonferroni correction for multiple testing. A FDR or Bonferroni adjusted p-value <0.05 will be considered significant. After DMRs are determined, Z-score transformation of the read count data will be applied for unsupervised hierarchical clustering analysis. Pathway analyses will be performed using <http://geneontology.org>.

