## 8. Statistical analysis

### 8.1 Main study parameter/endpoint:

DMRs specific for preeclampsia, intrauterine growth restriction and spontaneous preterm birth and uncomplicated pregnancies in first trimester residual NIPT samples.

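### The residual-NIPT sub-study promises disease-specific DMRs, but it states only disease-versus-control comparisons, has no rule for combined disease, and names preterm birth more narrowly than the cohort it should validate

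*Protocol*

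**What the plan says.** **Endpoint.** Section 8.1 of the residual-NIPT sub-study gives the main parameter as "DMRs specific for preeclampsia, intrauterine growth restriction and spontaneous preterm birth and uncomplicated pregnancies in first trimester residual NIPT samples". Its protocol summary also hypothesises that disease-specific DMRs are already present at the end of the first trimester.

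**Comparisons.** The summary sets out three disease groups, "all as compared to uncomplicated pregnancies (group 4". Section 5.1 repeats this: "preeclampsia, intrauterine growth restriction or spontaneous preterm birth compared to uncomplicated control pregnancies". Section 4.1 says the same. No section states a contrast between two disease groups or a criterion for calling a DMR specific. For significance, section 5.1 states: "A FDR or Bonferroni adjusted p-value <0.05 will be considered significant".

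**Groups.** Section 4.2 requires "Developed preeclampsia (n=20) or intrauterine growth restriction (n=20) or delivered spontaneously preterm (n=20) or had an uncomplicated pregnancy (n=20". Section 4.3 lists no exclusions. On numbers, section 4.1 states: "We aim to include samples from twenty women per group (total n=80". Section 4.4 splits each group of twenty into ten for training and ten for internal validation, and treats ten as the minimum for a stable set of DMRs.

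**Link to Addendum 3.** Section 1 says: "DNA methylation profiles related to preeclampsia, intrauterine growth restriction or spontaneous preterm birth identified in NIPT samples can serve as a validation cohort". What is to be validated is the prospective cfDNA cohort within Predict, and section 2 makes this an objective. Addendum 3 (Implementation) gives its own outcome as DMRs between "uncomplicated controls versus women who develop pregnancy related diseases like pre-eclampsia, intra-uterine growth restriction and pre-term birth". It assumes a 9% incidence of preterm birth, 300 women and 20-25% loss, and expects at least ten preterm cases.

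**The concern.** A region that differs between pre-eclampsia and controls is associated with pre-eclampsia. It may differ just as much in growth restriction. With only disease-versus-control lists, *specific* can mean no more than present in one list and absent from the others. Absence from a list of significant results is not evidence of no effect, least of all with ten training samples per group. A region shared by several diseases could then be reported as a marker of one.

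Two further points bear on the same endpoint. Pre-eclampsia with growth restriction fits two of the four groups, and nothing says which one the woman joins. Selection runs until each group is full, so the choice is left open at the moment it matters. For preterm birth, profiles from spontaneous cases would be set against a cohort whose preterm cases are not limited to spontaneous ones. A failure to replicate could then reflect case mix and not a false finding.

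**Working it through.** **1. The plan's own figures.** 4 groups × 20 = 80, and 10 + 10 = 20. Both agree with sections 4.1 and 4.4. The protocol states that power cannot be calculated, so there is no power figure to reproduce.

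**2. Endpoint against contrasts.** Sections 8.1 and the summary ask for regions specific to a disease. The summary and sections 4.1 and 5.1 name only disease-versus-control comparisons. The hierarchical clustering in section 5.1 is unsupervised and follows the determination of DMRs, so it does not test one disease against another.

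**3. How often a shared region looks specific.** This is an illustration by normal approximation, not the planned Chi-squared test on read counts.

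- Two disease groups and one control group have equal size and variance. The two contrasts share the controls, so their correlation is 1/(1 + 1) = 0.5. This is the same for ten or twenty per group.
- The true effect is the same in both diseases, and each contrast has power *p* (assumed). With a = Φ⁻¹(p), the probability that both are significant is B = Φ₂(a, a; 0.5), ignoring significance in the wrong direction.
- The probability that exactly one is significant is 2(p − B).
- At p = 0.5, B = 1/4 + arcsin(0.5)/(2π) = 1/3, which gives 2(1/2 − 1/3) = 0.33.

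| Assumed power | Both lists (B) | Exactly one list, 2(p − B) |
|---|---|---|
| 20% | 0.087 | 0.23 |
| 50% | 0.333 | 0.33 |
| 80% | 0.687 | 0.23 |
| 90% | 0.832 | 0.14 |
| 95% | 0.912 | 0.08 |

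For a given power, a fixed significance threshold does not enter the formula.

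**4. Women with two conditions.** Let *f* be the share of a case group with a second study condition (assumption; the protocol gives none). The single-condition women in a set of ten number 10(1 − f): 9, 8 and 7 at f = 10%, 20% and 30%. All are below the protocol's own minimum of ten, which argues against simply dropping these women without replacing them.

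**5. Preterm birth in Addendum 3.**

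- Women followed: 300 × 0.75 = 225 to 300 × 0.80 = 240.
- Preterm births: 225 × 0.09 = 20.3 to 240 × 0.09 = 21.6.
- Spontaneous at 50% (assumption): 10.1 to 10.8. The binomial probability of at least ten is 0.56 to 0.64.
- Spontaneous at 70% (assumption): 14.2 to 15.1. The probability of at least ten is 0.91 to 0.94.

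**The case against.** *Specific* may be loose wording. Section 8.1 also speaks of DMRs specific for uncomplicated pregnancies, section 2 asks for DMRs related to adverse outcome, and the stated aim is each disease against controls. On that reading the planned contrasts do serve the aim. A reader might infer that the main endpoint is not tested at all, and that goes too far: association with each disease is tested. But the summary does say disease-specific, so the ambiguity stands and needs settling.

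A reader might also infer that one woman can be counted in two groups. The total of 80 implies that each is counted once. *Uncomplicated* keeps the study conditions out of the controls, and *spontaneous* should keep medically indicated deliveries out of the preterm group. What remains is mainly the unassigned woman with pre-eclampsia and growth restriction. Assignment detail may sit in an analysis plan that is not shown, but it governs selection, and eligibility is set in this protocol.

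The shared controls might be blamed for false specific findings. Their correlation works the other way for chance hits, which tend to appear in both lists.

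On preterm birth, neither sub-study gives an operational definition, so this is a difference in named scope, not two conflicting definitions. The expected number of spontaneous cases still reaches the ten that Addendum 3 has in mind, so no expected shortfall is shown.

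**Conclusion.** The point holds in this limited form. The protocol names a disease-specific endpoint and states only comparisons with controls, which cannot separate specific from shared regions. The probability that a region equally present in two diseases lands in only one list runs from 0.08 to 0.33 over an assumed power of 20% to 95%. The 0.33 is the maximum over power, reached at 50%, and should not be read as the expected rate. The figures also rest on equal group sizes, a normal approximation and equal true effects.

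The gap for combined pre-eclampsia and growth restriction is real, but its extent is unknown because the documents give no frequency. The preterm mismatch matters because validating the prospective subcohort is an objective. Its size depends on the spontaneous share, which is also assumed. For a pilot this should be corrected. It does not undermine the association results.

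**What to change.** 1. Keep the three disease-versus-control contrasts and add the disease-versus-disease contrasts on the same data. Call a DMR *specific* only if it also differs from the other case groups; otherwise report it as associated with the disease, or as shared. This needs no new samples. The cost is that fewer DMRs will be called specific, given ten training samples per group.
2. Before selection starts, fix which group a woman with both pre-eclampsia and growth restriction joins, and record the second condition. Repeat the contrasts without such women as a sensitivity analysis. Leaving them out of the main analysis would change the population and draw down a limited pool of stored samples.
3. Make the preterm validation comparison in the spontaneous subset of Addendum 3. Restate the expected number there: 20 to 22 preterm births in all, and about 10 to 15 spontaneous under a stated share of 50 to 70%, with a probability of about 0.56 to 0.94 of reaching ten. The cost is a smaller validation comparison and the need to record type of onset.
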